### Adverse events (AEs)

2.5

All adverse events (AEs) that occur between the surgery and 1 year post-surgery will be recorded. If necessary, the investigators will administer treatments. A serious AE (SAE) is defined as any adverse reaction resulting in any of the following outcomes: a life-threatening condition or death; a condition that requires inpatient hospitalization or prolongation of an existing hospitalization, threatening to cause disability or death; a congenital anomaly; or a birth defect. All SAEs will be reported to the IRB and certificated committee for regenerative medicine by the responsible investigator.

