**Methods/design::**

This phase 1 first-in-man study is an open-label, single-center, two-step dose escalation study. A total of 6 patients, who had no recurrence of head and neck cancer over 5 years following radiation therapy and suffered from radiation-induced xerostomia, will receive a transplantation of E-NMCs derived from autologous PBMNCs to a submandibular gland. The duration of the intervention will be 1 year. To analyze the recovery of salivary secretion, a gum test will be performed. To analyze the recovery of atrophic salivary glands, computed tomography (CT), and magnetic resonance imaging (MRI) of salivary glands will be conducted. The primary endpoint is the safety of the protocol. The secondary endpoints are the changes from baseline in whole saliva secretion and salivary gland atrophy.

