### Exclusion criteria

2.3

The patients who participate in this study will be required to undergo blood collection for the isolation of PBMNCs. Patients who show low hemoglobin counts will thus be excluded: <12.5 g/dl for males and <12.0 g/dl for females when 200 ml blood collection is conducted, and <13.0 g/dl for males and <12.5 g/dl for females when >200 ml blood collection is conducted. The other major exclusion criteria are as follows:

1.xerostomia caused by a salivary gland tumor;2.any other malignancy or sepsis;3.severe autoimmune or endocrinological disease;coagulation abnormality (PT < 50% or outside the APTT range 23.5–42.5 seconds);4.positivity of syphilis test/HBV antigen/HCV antigen/anti-HTLV-1 antibody/anti-HIV antibody;5.liver dysfunction (higher or lower value of 2 biomarkers of liver function than the following criteria: AST 10–40 IU/L, ALT 5–45 IU/L);6.pregnancy;7.risk of allergy regarding the drug used in this study;8.allergy regarding penicillin G, amphotericin B, or streptomycin;9.transmissible spongiform encephalopathy;10.dementia;11.a psychiatric disorder such as depression;12.a smoking habit;13.being judged by the clinical investigator as an inappropriate patient for this study.

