**Figure 2 F2:**
[figure not shown]
Treatment schedule and outcome measures. CT = computed tomography, MRI *=* magnetic resonance imaging, PBMNCs = peripheral blood mononuclear cells, E-MNC = effective mononuclear cell.

The primary endpoint is the safety/tolerability of the protocol. The safety assessment, which conducted by independent safety monitoring board, will be done by a two-step process. The first 3 enrolled patients will receive transplantation of a low dose of E-MNCs (8 × 10^6^), and their safety will be assessed at ≥4 weeks after the surgery. If there are no serious adverse events in any of these 3 patients, the next 3 patients enrolled will receive transplantation of a high dose of E-MNCs (2 × 10^7^), and their safety will be assessed.

The secondary endpoints are the change from baseline in salivary secretion assessed by gum tests and the change in salivary gland atrophy (i.e., the rate of atrophic parts in salivary glands, and the volume of atrophic glands) assessed based on the CT/MRI findings.

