### Method for the generation of E-MNCs

2.6

The generation of E-MNCs, specific conditions of which were established by CellAxia Inc. (Tokyo, Japan), will take place under sterile conditions in a cell-processing center (CPC) at Nagasaki University Hospital. With the method to be used, 100 to 240 ml of peripheral blood is obtained and PBMNCs are separated by density gradient centrifugation with the use of a separation medium (Histopaque-1077, Sigma Aldrich, St Louis, MO). The isolated PBMNCs are seeded on 6-well Primaria tissue culture plates (BD Biosciences, San Jose, CA) at a density of 4 × 10^6^ cells/3 ml of medium/well and cultured for 6 to 7 days under the 5G-culture system as previously described.^[8]^

Briefly, PBMNCs are cultured in serum-free medium (Stemline II Hematopoietic Stem Cell Expansion Medium; Sigma Aldrich) with recombinant human stem cell factor (SCF), recombinant human Fms-related tyrosine kinase 3 (Flt-3) ligand, recombinant human thrombopoietin (TPO), recombinant human vascular endothelial growth factor (VEGF), and recombinant human interleukin-6 (IL-6) (all from Peprotech, Rocky Hill, NJ), which is modified human quality- and quantify-controlled culture system as described in our previous work.^[8,9]^ After 6 or 7 days of cultivation, the cells (effectively conditioned PBMNCs; E-MNCs) are harvested.

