### Evaluation of E-MNCs

2.7

Quality testing on cell appearance is executed at 5 days of cultivation before harvesting of E-MNCs. Then, at 6 or 7 days, harvested E-MNCs are assessed for viable cell number, viability, and the presence of the macrophage fraction via flow cytometry, and then it is decided whether or not to administer E-MNCs to patients. Quality testing for E-MNCs also includes the presence of bacteria, virus, mycoplasma, or endotoxin contamination.

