## Discussion

3

For the restoration of radiation-induced atrophic salivary glands, experimental approaches applying cell-based therapy have recently been investigated.^[10–13]^ Among these approaches, intra-glandular or -venous injections of mesenchymal stem cells (MSCs) in an irradiation mouse model have been examined frequently and show the potential of this strategy to slow the atrophic process.^[12]^ MSCs can display paracrine effects via releasing anti-inflammatory, vasculogenic, and anti-apoptotic cytokines to damaged glands, and these effects induce the anti-inflammatory phenotypes of activated macrophages at injured sites.^[14,15]^ Such macrophages function in neo-vascularization and subsequent tissue regeneration.^[16–18]^ These experimental approaches strongly suggest that cell-based therapies are promising as an alternative remedy for atrophic salivary glands. Indeed, more recently, Grønhøj et al have used adipose tissue-derived MSC therapy in a clinical study and demonstrated efficacy in a phase 1/2 trial for radiation-induced xerostomia.^[19]^ However, the autologous cell sources reported to date such as bone marrow, adipose tissue, or dental mesenchymal tissue require invasive procedures to harvest at the donor site.^[11,20,21]^ In addition, securing a sufficient number of highly functional MSCs in culture to ensure their therapeutic effects remains a challenge, particularly for elderly patients.^[22,23]^ Therefore, as an alternative strategy, we have developed a novel culture method to obtain therapeutic cells from a readily available and low invasive source, the peripheral blood. E-MNCs may affect the restoration of atrophic tissues more directly than MSCs, because E-MNCs contain an enriched population of M2 macrophage-like cells, which have similar properties to anti-inflammatory macrophages induced by transplanted MSCs at injured sites.

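### Adverse event recording opens at surgery, so non-serious events between blood collection and surgery fall outside the window for a primary endpoint defined as safety of the protocol

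*Protocol article*

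**What the plan says.** Section 2.5 (Adverse events) states the recording rule: "All adverse events (AEs) that occur between the surgery and 1 year post-surgery will be recorded". Section 2.8 describes the surgery as the ultrasound-guided injection into one submandibular gland, so it does not include the blood draw.

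The endpoint is worded more broadly. The Abstract says "The primary endpoint is the safety of the protocol", and section 2.4 says "The primary endpoint is the safety/tolerability of the protocol".

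Three study steps come before surgery:

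- **Collection.** Section 2.3: "The patients who participate in this study will be required to undergo blood collection for the isolation of PBMNCs". The same section sets haemoglobin exclusion limits that depend on the volume drawn. Section 2.6 gives the volume: "100 to 240 ml of peripheral blood is obtained".
- **Culture.** Section 2.6: "After 6 or 7 days of cultivation, the cells (effectively conditioned PBMNCs; E-MNCs) are harvested".
- **Release decision.** Section 2.7 lists the tests on the harvested cells, and "then it is decided whether or not to administer E-MNCs to patients".

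The visits named in the text of section 2.4 are a baseline visit about one month before surgery and specified days after it. No visit at blood collection is named there. Figure 2, the schedule, is not available in the text reviewed.

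**The concern.** The recording rule and the endpoint do not cover the same span. A first-in-man trial whose endpoint is the safety of the protocol should record harms from every procedure that the protocol imposes, and the blood draw is one of them. The haemoglobin limits show that the authors themselves treat it as an exposure that needs care. Events such as fainting, haematoma or a fall in haemoglobin would be expected at or soon after the draw, and so before the window opens.

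The release decision adds a second gap. A patient whose cells fail testing has been bled for the study but has no surgery, so under the stated rule the window never opens for that patient. The safety record is then conditional on successful manufacture.

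At stake is how complete the tolerability part of the primary endpoint is. With only six patients to be transplanted, one unrecorded event would noticeably change that description.

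**Working it through.** The article gives no calculation on this point to reproduce. The check sets the order of events against the window, and some illustrative arithmetic follows.

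**1. Timeline, with surgery as day 0**

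| Step | Time | Source | In the stated window? |
|---|---|---|---|
| Blood collection | about day −7 or −6 | inferred from the culture time in 2.6 | No |
| Culture | 6 to 7 days | 2.6 | No |
| Harvest, testing, decision to inject | about day 0, before injection | 2.7 | No |
| Injection | day 0 | 2.8 | Yes, window opens |
| Follow-up | to 1 year | 2.5 | Yes |

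The article does not state the interval from collection to injection. The table assumes injection on the day of harvest; a later injection would widen the gap. The Discussion gives 5 to 7 days for obtaining the cells, which would allow day −5.

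**2. Share of time uncovered** = gap / (gap + 365)

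- 5 days: 5/370 = 1.35%
- 6 days: 6/371 = 1.62%
- 7 days: 7/372 = 1.88%

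The share of time is small, but the whole collection procedure lies within it.

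**3. Chance of at least one collection-phase event in six patients** = 1 − (1 − p)^6. The rate p is an assumption; the article gives none.

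| Assumed p per patient | Chance of at least one in 6 |
|---|---|
| 1% | 5.9% |
| 2% | 11.4% |
| 5% | 26.5% |
| 10% | 46.9% |

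Of these events, the non-serious ones with onset before surgery would go unrecorded under section 2.5.

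**4. Patients bled but not transplanted.** Assume a release-failure rate q, also not in the article. The expected number bled for six transplanted is 6/(1 − q), and the chance of at least one failure before six are transplanted is 1 − (1 − q)^6.

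| Assumed q | Expected number bled | Chance of at least one bled but not transplanted |
|---|---|---|
| 5% | 6.3 | 26.5% |
| 10% | 6.7 | 46.9% |
| 20% | 7.5 | 73.8% |

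The tables in steps 3 and 4 show a range only. The mismatch follows from step 1 and does not depend on them.

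**The case against.** The strongest case against is that the article's purpose is narrower than its endpoint wording. The Introduction gives the objective as the safety of injecting the cells into the gland. The specific risks named in the Discussion, a newly developed cell-processing method and possible promotion of tumour growth or metastasis, belong to the injected product. A window that opens at surgery suits that purpose. This has force, and limiting the endpoint to the injection would also remove the inconsistency. But the endpoint is worded as safety of the protocol in both the Abstract and section 2.4, and narrowing it would leave a required procedure with no planned record of non-serious harm.

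A second objection is that this is a detail condensed out of a journal article. That does not hold: the article does not omit a start of recording, it states one.

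A reader might go further and infer any of the following, which the document does not support:

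- **That every harm from collection is lost.** Collection-related harm that first appears after surgery is inside the window. The sentence on reporting serious adverse events has no start date, so a serious collection event may still be reported. Section 2.4 also requires a safety assessment at each visit. If the unseen schedule includes a collection visit, some events could be noted there, although the window in section 2.5 would still exclude them.
- **That the escalation decision is compromised.** It depends on serious adverse events in the first three patients, assessed at least four weeks after surgery. Non-serious collection events could not change it.
- **That the trial fails to prove that the harvest is gentle.** The Discussion does call the cell source "a readily available and low invasive source, the peripheral blood", but this is background argument and not an endpoint or hypothesis.
- **That the cohorts must be redefined or a patient flow laid out.** These matters are commonly left to the full protocol or analysis plan, so their absence from the article is not a fault.

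**Conclusion.** The point holds in a limited form. As written, section 2.5 leaves out non-serious adverse events with onset between blood collection and surgery, and those of any patient bled but never transplanted, while the primary endpoint is the safety and tolerability of the protocol. The gap is about 6 to 7 days per transplanted patient, inferred from the culture time (5 to 7 days by the Discussion) and assuming injection on the day of harvest.

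How many events would be missed cannot be derived from the article, because it gives neither an event rate nor a release-failure rate. The weight is moderate: the description of tolerability is incomplete, but the reporting of serious events and the escalation rule are largely untouched.

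**What to change.** Reword section 2.5 so that all adverse events are recorded from the start of blood collection to one year after surgery. For a patient who is bled but not transplanted, record them through a stated end of follow-up. Report two periods separately:

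- collection to surgery, with all patients bled as the denominator;
- surgery to one year, with the transplanted patients as the denominator.

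The cost is a short amendment and about one extra week of recording per patient. The text names no visit at collection, so the amendment should also say where these events are entered. Section 2.10 puts the start of recruitment at April 2019. For patients already treated, collection-phase events would have to be sought in source records, and the report should mark them as gathered retrospectively.

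### The SAE definition is written in terms of adverse reactions and has a garbled outcome list, so some serious events may lose the SAE label, escape SAE reporting and possibly not count in the escalation check

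*Protocol article*

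**What the plan says.** Section 2.5 (Adverse events) of the protocol article first sets a broad recording rule: "All adverse events (AEs) that occur between the surgery and 1 year post-surgery will be recorded". No causality filter is attached. Seriousness is then defined with a different noun: "A serious AE (SAE) is defined as any adverse reaction resulting in any of the following outcomes". The list that follows begins with fatal and life-threatening outcomes and ends with congenital defects. Between them stands the item on admission to hospital, which reads: "a condition that requires inpatient hospitalization or prolongation of an existing hospitalization, threatening to cause disability or death". The section closes by requiring the responsible investigator to report every SAE to the ethics board and the regenerative-medicine committee.

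Section 2.4 (Outcome measurements, text after Figure 2) uses the same category to control escalation: "If there are no serious adverse events in any of these 3 patients, the next 3 patients enrolled will receive transplantation of a high dose". The step-1 assessment takes place at 4 weeks or later and is made by an independent safety monitoring board. The same section states the main outcome broadly: "The primary endpoint is the safety/tolerability of the protocol".

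**The concern.** Within one paragraph the text moves from event to reaction. If reaction carries its usual meaning, an event must be attributed to treatment before it can be serious in the sense of this protocol. A serious event judged unrelated would then be an adverse event but not an SAE.

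The outcome list adds a second narrowing. As punctuated, the phrase about threatening disability or death belongs to the hospitalization item and may qualify it, so an ordinary admission might not count. Disability appears only as something threatened, never as something that has happened.

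Two operative rules use this definition: the reporting duty in section 2.5 and the condition for moving to the higher dose in section 2.4. The second rests on three patients, so the label given to one event can decide it. The study is open-label with no control group, and every participant has had head and neck cancer, so attribution to the underlying disease is an easy judgement to make. The Discussion itself names tumour growth and metastasis as a potential risk of the product. Over the year of follow-up, that is the kind of event whose label would turn on attribution.

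**Working it through.** **Step 1: the text.** The document states no event rate, power or error rate for the escalation condition, so there is no figure to reproduce. The main check is to set the provisions side by side.

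| Provision | Term used | Consequence for a serious event judged unrelated, read literally |
|---|---|---|
| 2.5, recording | adverse event | recorded |
| 2.5, definition of serious | adverse reaction | not an SAE |
| 2.5, reporting | SAE | not covered by the stated duty |
| 2.4, escalation | serious adverse event | unclear: the term says event, its definition says reaction |
| 2.4, primary endpoint | safety/tolerability | still included |

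The hospitalization item has two readings. In the first, the closing phrase qualifies admission, and an admission that threatens neither disability nor death is not serious. In the second, a separator was lost, and the phrase is a further item of its own. On neither reading does disability that has occurred have its own item.

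**Step 2: possible size of the effect on escalation.** This is an illustration. Inputs:

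- n = 3 patients in step 1, and escalation if none has an SAE (section 2.4).
- p = a patient's risk of at least one serious event by the step-1 assessment. Assumed.
- f = the share of those patients whose event is judged related. Assumed.

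If all serious events count, P(pass) = (1 − p)³. If only related ones count, P(pass) = (1 − pf)³. Patients are treated as independent.

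With f = 0.5:

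- p = 0.05: 0.95³ = 0.857 against 0.975³ = 0.927, a gap of 7 percentage points.
- p = 0.10: 0.90³ = 0.729 against 0.95³ = 0.857, a gap of 13 points.
- p = 0.20: 0.80³ = 0.512 against 0.90³ = 0.729, a gap of 22 points.

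Sensitivity to f:

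| p | all count | f = 0.75 | f = 0.50 | f = 0.25 |
|---|---|---|---|---|
| 0.05 | 0.857 | 0.892 | 0.927 | 0.963 |
| 0.10 | 0.729 | 0.791 | 0.857 | 0.927 |
| 0.20 | 0.512 | 0.614 | 0.729 | 0.857 |

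For any p above 0 and f below 1, (1 − pf)³ exceeds (1 − p)³. The direction is therefore fixed: a relatedness filter can only make the condition easier to meet.

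**The case against.** Four counter-arguments deserve an answer.

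**A language slip.** Adverse reaction is never defined, nothing says unrelated events are excluded, section 2.4 itself says event, and the article's English is loose in other places. A slip is plausible. This stands and lowers confidence, but it does not remove the need for correction: if event was meant, one word has to change; if reaction was meant, section 2.4 does not mean what it appears to say.

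**Article condensation.** A journal article may leave detail to the full protocol. This stands for the absence of an item for other medically important events, which is not pressed here. It does not cover the definition itself, which is stated in the article and is ambiguous as stated.

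**The primary endpoint and the board.** A reader might infer that unrelated serious events drop out of the primary endpoint. The documents do not support that: the endpoint is overall safety/tolerability, all adverse events are recorded, and a safety assessment is made at every visit. A reader might also infer that causality is settled before the independent board sees an event. The article does not say who judges causality, when, or what the board receives.

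**The rates.** Neither p nor f is in the document. The procedure is a 400 μl ultrasound-guided injection under local anaesthesia in patients in complete remission 5 years after radiotherapy, and the step-1 assessment may come as early as 4 weeks. Nothing there supports a high p, so the lower rows of risk carry more weight. For the same reason tumour recurrence is a weak argument about the step-1 decision, though it remains relevant to reporting over the year.

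**Conclusion.** The concern holds in a limited form. As worded, section 2.5 can withhold the SAE label from serious events judged unrelated, from some hospitalizations and from disability that has occurred. The consequence for SAE reporting follows directly from the literal text. The consequence for escalation is possible but not certain, because sections 2.4 and 2.5 use different terms. The events stay in the safety data throughout.

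On the escalation condition, the chance of passing would rise by about 7 to 22 percentage points for per-patient risks of 5% to 20% if half of serious events are judged related. Those figures rest wholly on assumed rates, and the effect shrinks as p falls or f approaches 1. This should be fixed; confidence is moderate because the wording may be a translation slip.

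**What to change.** In section 2.5:

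- Define an SAE as an adverse event with a listed outcome, whether or not it is judged related to treatment.
- List the outcomes as separate alternatives, with hospitalization or its prolongation standing alone and disability standing alone.
- Record causality as a separate field, outside the definition of seriousness.

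Reconcile sections 2.4 and 2.5 so that the text says explicitly which events the condition "If there are no serious adverse events in any of these 3 patients" counts. That choice belongs to the sponsor and the safety board; this review does not make it.

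The cost is one revised paragraph, one clarifying sentence and, if not already present, one case report form field. The downside is slightly more SAE reporting and board review, including for events that prove unrelated.

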### Method for the generation of E-MNCs

2.6

The generation of E-MNCs, specific conditions of which were established by CellAxia Inc. (Tokyo, Japan), will take place under sterile conditions in a cell-processing center (CPC) at Nagasaki University Hospital. With the method to be used, 100 to 240 ml of peripheral blood is obtained and PBMNCs are separated by density gradient centrifugation with the use of a separation medium (Histopaque-1077, Sigma Aldrich, St Louis, MO). The isolated PBMNCs are seeded on 6-well Primaria tissue culture plates (BD Biosciences, San Jose, CA) at a density of 4 × 10^6^ cells/3 ml of medium/well and cultured for 6 to 7 days under the 5G-culture system as previously described.^[8]^

Briefly, PBMNCs are cultured in serum-free medium (Stemline II Hematopoietic Stem Cell Expansion Medium; Sigma Aldrich) with recombinant human stem cell factor (SCF), recombinant human Fms-related tyrosine kinase 3 (Flt-3) ligand, recombinant human thrombopoietin (TPO), recombinant human vascular endothelial growth factor (VEGF), and recombinant human interleukin-6 (IL-6) (all from Peprotech, Rocky Hill, NJ), which is modified human quality- and quantify-controlled culture system as described in our previous work.^[8,9]^ After 6 or 7 days of cultivation, the cells (effectively conditioned PBMNCs; E-MNCs) are harvested.

